#### Analysis of brain function and structure before vs. after BLT

Brain function and structure will be analyzed between pre- vs. post-BLT intervention in the whole sample of 60 participants at the Leiden study site.

For the structural parameters of GM, the longitudinal two-stage analysis framework of general linear modelling (GLM) will be used. This is implemented as an automated analysis pipeline in the longitudinal data analysis framework of FreeSurfer. In brief, this method first extracts the regional GM parameters (VOL, SA, THK, and LGI) at the level of each subject and each brain point (vertex) for each hemisphere separately. In a second step, a group level analysis will be performed by using a repeated measures ANOVA. Hereby, we will compare the structural parameters THK, VOL, SA, and LGI between pre- and post- BLT while including age, sex, and treatment arm (*Light@Home, LightCafé, LightCafé +*) as covariates and to correct for their potential confounding effects. To account for multiple testing across the whole brain, we will perform Monte Carlo simulations with 10,000 iterations to identify significant contiguous clusters of vertex-wise group differences (*p* < 0.05).

For the analysis of the structural WM properties of main WM tracts, the probabilistic tractography pipeline TRACULA will be used. This automatic pipeline is first pre-processing the DTI images (correcting for image distortions, eddy currents, and B0 field inhomogeneities). Afterwards, head motion measures are extracted which can be used in further statistical analysis as covariates, co-registration of DTI and anatomical images is performed, the registration of individual images to a common space occurs, then the probabilistic distributions of 42 major WM fiber tracts are reconstructed from which the main properties of WM bundles can be extracted (FA and MD). Then the pipeline enters the longitudinal analysis stream which involves as a main statistical approach, the earlier mentioned GLM model. Hence, a repeated measures analysis of variance (ANOVA) will be performed on group level in which the comparison of FA and MD between pre- and post-BLT will be evaluated. Afterwards, clusterwise correction for multiple comparisons using Monte Carlo simulations with 10,000 iterations will be employed to account for multiple testing effects.

For the analysis of brain function, the connectivity maps of main functional resting state networks will be analyzed using the CONN toolbox [104] from the software Statistical Parametric and Mapping (SPM). For this, we will replicate the study by [59] [59]. Hence, we will both investigate inter-network connectivity (in DMN, FPN, SMN, SN) but also at the intra-network connectivity as a post hoc test using a graph analysis. In the first level analysis, the network properties of each network in each subject will be established. In the second level analysis, a group-level analysis will be performed to analyze the differences in the brain networks (DMN, FPN, SMN, SN) between pre- and post-BLT. A significance threshold of 0.05 will be set and a false discovery rate (FDR) correction method will be applied to correct for multiple comparisons.

#### Analysis of functional and structural brain correlates and clinical symptoms

To assess whether the encountered brain changes are linked to the clinical symptom improvement, multiple regression analysis will be performed. Hence, brain measures (functional or structural) which showed changes between the pre- vs post-BLT intervention will be correlated with the clinical symptom change scores of depression (QIDS-SR, MADRS). More specifically, the brain measures involved are functional connectivity measures of specific brain networks (DMN, FPN, SMN, SN) which showed changes between pre and post BLT, the structural measures—GM properties (THK, VOL, SA) but also WM tracts properties (FA, MD) which showed changes between pre-post BLT.

Analysis of melatonin and BLT linked brain changes.

We will evaluate if a change in DLMO is also linked to the encountered brain changes on functional and structural level. Hence a multiple regression analysis will be performed between the encountered brain changes as predictors (in function and structure) and the DLMO changes as outcome measure in the analysis.

To evaluate the potential link between circadian light sensitivity and brain alterations in depression, a multiple regression analysis will be performed. Hence the melatonin suppression will be used as a predictor and functional and structural brain changes and as outcomes in the model.

### Interim analyses {21b}

N/a—we are not conducting any interim analyses.

### Methods for additional analyses (e.g., subgroup analyses) {20b}

Exploratory subgroup analyses will be conducted to examine variations in the effects of different administration strategies on depressive symptoms, sleep, and circadian rhythms across various depression diagnoses. Additionally, the whole brain structure and functional parameters will be compared between the three treatment arms. As a post hoc explorative analysis the functional and structural brain parameters will be compared between remitters vs non-remitters. Multiple comparison corrections for repeated measures will be done.

Furthermore, we will explore the relationship between treatment adherence (as measured by self-report and light sensor data) and treatment effectiveness. Adherence will be operationalized as the percentage of completed light therapy sessions (based on sensor data, the timing of light exposure relative to the prescribed schedule, and daily self-reported compliance). These adherence indicators will be added as covariates in regression models predicting changes in depressive symptoms, sleep, and circadian phase markers. Primary outcome models will also include medication type and dose as time-varying covariates to test for interaction with BLT. Exploratory subgroup comparisons (e.g., on versus off antidepressant) may further probe whether concurrent treatments alter BLT’s therapeutic impact.

### Methods in analysis to handle protocol non-adherence and any statistical methods to handle missing data {20c}

The data analysis is an intent-to-treat analysis with participants analyzed as randomized, regardless of adherence to the treatment protocol. Additionally, completer analyses will be conducted, including only those participants who have both pre-treatment and post-treatment data. Furthermore, per protocol analyses will focus on participants who completed at least 80% of the treatment (i.e., attending 4 out of 5 days of BLT per week). Any substantial differences between these analytical approaches will be evaluated and reported.

We will describe the extent and patterns of missing MADRS scores and covariates overall and by treatment arm. To evaluate whether missingness is completely at random (MCAR), we will apply Little’s MCAR test and examine associations between missingness and key variables (e.g., age, sex, diagnosis, depression severity, treatment expectancy). Under a plausible missing-at-random (MAR) assumption, we will perform multiple imputation by chained Eqs. (10 imputations) as a sensitivity analysis, refitting the primary multilevel mixed-effects models in each imputed dataset and pooling estimates via Rubin’s rules. We will then compare results from the complete-case analysis and the MAR sensitivity analysis to our main intent-to-treat (observed-data) findings. Any notable discrepancies in effect estimates, model fit, or inferential conclusions across these approaches will be reported.

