### Intervention description {11a}

In all study arms, participants are subjected to BLT in adherence to Dutch BLT guidelines [72], utilizing an Innolux LED light Lamp delivering light with an illuminance of 10,000 lx at a distance of 70 cm and a color temperature of 3800 K. BLT sessions, lasting 30 min each, are scheduled from Monday to Friday between 7:30 AM and 10:30 AM.

The number of BLT sessions is contingent upon the individual response of each participant, with a maximum duration of 3 weeks. Initially, participants undergo five consecutive BLT sessions during the workweek. Subsequently, the therapeutic efficacy is evaluated utilizing the QIDS-SR during the Friday session. If the QIDS-SR falls below 6, remission is inferred, leading to the termination of BLT. Alternatively, an additional five sessions are administered. This evaluation and decision process is repeated at the end of the second week. If the QIDS-SR score is still above 6, a third and final week of treatment is provided.

This individualized strategy is intended to reduce the small risk of (hypo)manic switches, which occur in less than 2% of bipolar patients and almost exclusively in those not maintained on mood stabilizers [11, 73]. We will continuously monitor for (hypo)manic symptoms using the Young Mania Rating Scale (YMRS; [74]) and clinical observation: a YMRS score ≥ 13 and clinician‐identified symptoms will lead to immediate treatment cessation, while scores of 10–11 will prompt a joint review with a second clinician to decide on discontinuation [75, 76].

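### The per-protocol set is defined by two rules that disagree beyond one week of treatment, and the weekly rule favours fast remitters because response sets treatment length

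*Protocol article*

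**What the plan says.** Under the section on non-adherence and missing data {20c}, the main analysis is intention-to-treat. A completer analysis and a per-protocol analysis are added, and substantial differences between the approaches are to be evaluated and reported. The per-protocol set consists of "participants who completed at least 80% of the treatment (i.e., attending 4 out of 5 days of BLT per week".

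The treatment itself has no fixed length. Intervention description {11a} states: "The number of BLT sessions is contingent upon the individual response of each participant, with a maximum duration of 3 weeks". It begins with a common block: "Initially, participants undergo five consecutive BLT sessions during the workweek". After the Friday QIDS-SR: "If the QIDS-SR falls below 6, remission is inferred, leading to the termination of BLT". Otherwise: "Alternatively, an additional five sessions are administered". After the second week: "If the QIDS-SR score is still above 6, a third and final week of treatment is provided". The Treatment phase section confirms that participants receive one, two or three weeks.

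**The concern.** The 20c sentence joins an overall percentage and a weekly count as if they were the same rule. They coincide only for someone treated for one week. For everyone else they define different analysis sets, and nothing in the text says which one governs, so the choice could be made after the data are seen.

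Under the weekly rule, the number of tests a participant must pass depends on how quickly the depression responded. A week-1 remitter passes once. Anyone treated for three weeks, including a week-3 remitter, passes three times. Two people equally willing to attend then have different chances of inclusion, and the difference follows QIDS-SR response. The questionnaire section reports a correlation above 0.80 between the QIDS-SR and the MADRS, so this is selection on a close correlate of the primary outcome.

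At stake is the promised comparison of per-protocol with intention-to-treat results. If attendance differs between home and café, the arms are filtered towards fast remitters to different degrees, and a per-protocol difference could be partly an artefact of the rule.

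**Working it through.** **Inputs from the article.** Five sessions per week; one, two or three weeks by response; threshold 80%, glossed as 4 of 5 days per week.

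**Assumptions.** The article gives no attendance rate or weekly remission rate. Attendance per session, p, is taken from 0.80 to 0.95, independent between sessions and unrelated to response.

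**The plan's own figure.** 4/5 = 80%, so the two rules agree for one week. In total, 80% of 5, 10 and 15 sessions is 4, 8 and 12.

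**Where they part.** Attendance of 5, 4 and 3 days gives 12/15 = 80%, which passes the overall rule. The third week has only 3 days, so the weekly rule fails.

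**Chance of inclusion.**
- One week, both rules: q = P(X ≥ 4 | 5, p) = 5p⁴(1 − p) + p⁵. At p = 0.85, q = 0.3915 + 0.4437 = 0.835.
- k weeks, weekly rule: q to the power k. At p = 0.85, 0.835² = 0.698 and 0.835³ = 0.583.
- k weeks, overall rule: P(X ≥ 4k | 5k, p). At p = 0.85 and k = 3, P(X ≥ 12 | 15) = 0.823.

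| p | 1 week, both | 2 weeks, weekly | 3 weeks, weekly | 2 weeks, overall | 3 weeks, overall |
|---|---|---|---|---|---|
| 0.80 | 0.737 | 0.544 | 0.401 | 0.678 | 0.648 |
| 0.85 | 0.835 | 0.698 | 0.583 | 0.820 | 0.823 |
| 0.90 | 0.919 | 0.844 | 0.775 | 0.930 | 0.944 |
| 0.95 | 0.977 | 0.955 | 0.934 | 0.988 | 0.995 |

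The weekly rule favours one-week participants at every p below 1. The overall rule is close to neutral from about 0.85, and its direction reverses above about 0.86. If attendance varies between people (beta distribution, mean 0.85, a + b = 10), one-week v three-week inclusion is 0.81 v 0.61 under the weekly rule and 0.81 v 0.76 under the overall rule.

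**Arm comparison, scenario A.** Assume the same true course in both arms (25%, 20% and 55% treated for 1, 2 and 3 weeks) and attendance of 0.90 v 0.80. The share stopping after week 1 or 2 is 45% in each arm as randomised.
- Weekly rule, p = 0.90: (0.25 × 0.919 + 0.20 × 0.844)/0.825 = 0.483.
- Weekly rule, p = 0.80: (0.25 × 0.737 + 0.20 × 0.544)/0.513 = 0.571. The gap is about 9 points.
- Overall rule, p = 0.90: (0.25 × 0.919 + 0.20 × 0.930)/0.935 = 0.445.
- Overall rule, p = 0.80: (0.25 × 0.737 + 0.20 × 0.678)/0.676 = 0.473. The gap is about 3 points.

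**Arm comparison, scenario B.** Assume a constant weekly chance of remission giving 45% by three weeks in both arms: h = 1 − 0.55^(1/3) = 0.181. The outcome is remission within three weeks, with attendance again 0.90 v 0.80.
- Weekly rule: 47.4% v 54.3%, a gap of 6.9 points.
- Overall rule: 44.6% v 46.7%, a gap of 2.1 points.

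**When the gap vanishes.** With 45% remission and attendance of 0.85 in both arms, the gap is 0. With remission of 40% v 55% and attendance of 0.85 in both, the difference is 15.0 points as randomised and 15.3 per protocol under the weekly rule.

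**The case against.** The strongest reply is that the definition is coherent. The regimen is response-guided, so someone who attends 4 of 5 sessions and stops at remission has followed it. Selection on behaviour after randomisation comes with any per-protocol set, which is why intention-to-treat is the main analysis. This stands and limits the weight of the point. It does not remove the contradiction between the two rules, or the avoidable selection that the weekly one adds.

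Three stronger readings are tempting, and the article does not support them.

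- A reader might infer that the per-protocol arm comparison is biased outright. It is not shown to be. The bias needs the weekly reading and, to be material, attendance that differs by arm. The Discussion expects the café's social setting to help adherence but gives no figure. The gaps above are also in remission during treatment; no effect on the MADRS contrast has been derived.
- A reader might extend the argument to the exploratory models under additional analyses {20b}, where "Adherence will be operationalized as the percentage of completed light therapy sessions". That measure has no cut-off. Its expected value is p on 5 or 15 sessions, and only its precision changes (SD at p = 0.85: 0.160 v 0.092). The unequal hurdle does not carry over.
- A reader might say that only non-remitters need 12 sessions. Under either rule, week-3 remitters need at least 12 too.

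It can also be said that a set based on week 1 alone would admit someone who attended 4 of 15 sessions. That is fair, and it is why such a set suits a sensitivity analysis better than the definition itself.

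**Conclusion.** The inconsistency in 20c is certain and needs no assumption: the same participant can be in the set under one half of the sentence and out under the other. Under the weekly half, enrichment for fast remitters follows at any attendance below 100% in the independent-attendance model. Its size depends on attendance: one-week v three-week retention is 84% v 58% at 85% attendance, 74% v 40% at 80%, and 92% v 77% at 90%. The overall 80% rule largely avoids this (84% v 82% at 85% attendance).

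Distortion between arms is conditional. An assumed attendance gap of 90% v 80% gives a false 7 to 9 points in remission under the weekly rule and 2 to 3 under the overall rule, favouring the less adherent arm. If attendance and remission speed are equal across arms, it is zero. The point should be corrected, but it concerns a supplementary analysis and leaves the primary intention-to-treat result untouched.

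**What to change.** In 20c, delete the weekly gloss and define per protocol as attendance at no less than 80% of all sessions scheduled for that participant. State that sessions falling after a stop directed under the discontinuation criteria {11b} count as not scheduled rather than missed. Add one sensitivity per-protocol set requiring 4 of the 5 week-1 sessions. Week 1 is the only week scheduled for everyone, so inclusion there does not depend on treatment length (0.835 for fast and slow remitters alike at 85% attendance).

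The count of scheduled sessions also depends on what happens at a QIDS-SR score of exactly 6. Intervention description stops treatment below 6, while the Treatment phase section continues it only above 6. These passages must be reconciled.

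The cost is a wording change and one extra supplementary analysis on attendance data already planned for collection. The downside is that a single poor week no longer excludes a participant whose overall attendance reaches 80%.

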### Plans to give access to the full protocol, participant-leveldata, and statistical code {31c}

Participant-level data (from consenting participants) and the corresponding statistical code will be made available upon request. Parts of the data, i.e., data published in peer-reviewed journals will be stored in the public repository. The aim of this step is that other researchers can have access to include these datasets in meta-analyses, reviews, or similar or enable replication of our study. This data is pseudonymized and will not contain any personal information. The complete data set will be stored on the local research institutional research servers in a pseudonymized fashion. We will adhere to the requirements of the DataverseNL platform for data archiving.

### Composition of the data monitoring committee, its role and reporting structure {21a}

This study does not include a Data Monitoring Committee as BLT is a low-risk intervention and study procedures are straightforward and do not require ongoing oversight.

### Adverse event reporting and harms {22}

Adverse events (AE) are defined as any undesirable experience occurring to a subject during the study, whether or not considered related to BLT. All AE reported spontaneously by the subject or observed by the investigator, or their staff will be recorded. Additionally, a weekly screening of AE will be conducted. All AEs will be followed until they have abated, or until a stable situation has been reached. Depending on the event, follow-up may require additional tests or medical procedures as indicated, and/or referral to the general physician or a medical specialist.

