## Interventions

### Explanation for the choice of comparators {6b}

This study compares the effectiveness of three distinct BLT administration strategies for treating depression:

I.**Home-Based BLT (*****Light@Home*****)**: Patients receive BLT in their own homes.II.**BLT in LightCafé (*****LightCafé*****)**: Patients undergo BLT in a café-like environment (*LightCafé*), which emphasizes lifestyle improvements alongside the therapy.III.**Personalized BLT in the LightCafé (*****LightCafé +*****)**: Patients receive BLT in the *LightCafé*, with treatment timing tailored to their individual sleep–wake pattern and personalized timing of darkness with the use of BBG.

The *Light@Home* condition serves as an active control condition against which both other conditions will be evaluated. Given that our primary objective is not to measure the effectiveness of BLT in alleviating depressive symptoms per se, but rather to optimize its delivery, the inclusion of a placebo or treatment-as-usual condition in this trial is deemed unwarranted. To assess and possibly control for the difference in expectations of treatments, all participants will complete the Credibility/Expectancy Questionnaire (CEQ; [71]) before treatment onset.

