**Fig. 1 Fig1:**
[figure not shown]
The LightCafé is a café-style space where each participant receives BLT against a backdrop of restorative design elements (e.g., ample natural light, greenery, artwork, and clustered seating). Sessions include 5–10 min of one-on-one lifestyle coaching with professional and take-home workbooks for self-guided sleep-, exercise-, and nutrition-support. All trial participants in the LightCafé and LightCafé+ arms are treated in this setting. Photo: Boschdijk location, GGzE Eindhoven en de Kempen, Netherlands

Each BLT session in the *LightCafé* includes 5–10-min consultations with a professional nurse or psychologist, during which participants discuss various aspects of their lifestyle, such as sleep hygiene, exercise, nutrition, daily routines, social interaction, and overall healthy living. These brief consultations are integrated into the light therapy sessions to provide personalized guidance and support. Additionally, participants are provided with workbooks designed for independent use, enabling them to actively work on and improve their lifestyle habits outside of the sessions. The ultimate goal of the *LightCafé* approach is to foster a stable rest-activity pattern, promote a more active lifestyle, ensure a fulfilling daily routine, and encourage social interaction, all within a treatment environment that enhances the overall treatment experience.

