### Treatment phase

During the treatment phase, participants receive 1, 2, or 3 weeks of BLT within their assigned condition. Every Friday, depressive symptoms are assessed using the QIDS-SR, regardless of whether the participant received treatment that week. Treatment will be continued as long as QIDS-SR-score is higher than 6, with a maximum of 3 weeks. Treatment tolerability and mania symptoms are assessed using the YMRS after each week of BLT. EMA, actigraphy, and light logger usage continue throughout the treatment.

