			***Treatment***			
	*Intake*	*B1*	*Evaluation*	*PT1*	*F1*	*F2*
**Mini International Neuropsychiatric Interview (M.I.N.I.)** [69] ***(clinical diagnosis of psychiatric disorders)***	X					
**Sociodemographics**	X					
**Current Medications and Therapies **	X			X	X	X
**Quick Inventory of Depressive Symptomatology Self-Report (QIDS-SR)** [70] ***(Self-reported Severity of Depressive Symptoms)***	X	X	X	X	X	X
**Montgomery-Åsberg Depression Rating Scale (MADRS)** [78] ***(Clinician-rated Severity of Depressive Symptoms)***		X		X		
**Morningness-Eveningness Questionnaire (MEQ)** [86] ***(Chronotype – Morningness/Eveningness preference)***	X				X	
**Ultra Short Munich Chronotype Questionnaire (µMCTQ)** [87] ***(Chronotype – Sleep Timing)***	X	X		X	X	X
**Pittsburgh Sleep Quality Index (PSQI)** [84] ***(Subjective Sleep Quality)***		X		X	X	X
**Insomnia Severity Index (ISI)** [85] ***(Severity of Insomnia Symptoms)***		X		X	X	X
**Short Form Health Survey - 12 items (SF-12)** [82] ***(Health-related functional outcomes)***		X		X	X	X
**Mental Health Quality of Life (MHQoL)** [83] (***Quality of Life related to Mental Health***)		X		X	X	X
**Credibility/Expectancy Questionnaire (CEQ)** [71] ***(Treatment credibility and participant expectations)***		X				
**Adverse Event Scale** ***(Occurrence and severity of adverse events)***			X			
**Young Mania Rating Scale (YMRS)** [96] ***(Symptoms of (hypo)mania)***			X			

This table gives an overview of the questionnaires utilized at various assessment points in the Baseline, Treatment, and Follow-up. Each questionnaire’s purpose is indicated alongside the time points at which it was administered indicated with an X. No questionnaires are administered during melatonin assessments (M1, M2, M3) or MRI sessions (MRI-1, MRI-2)

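### The weekly AE screen covers every arm, but unsolicited AEs get daily staff contact in two arms only, and the solicited scale has no baseline and appears to follow treatment length

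*Protocol article*

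**What the plan says.** **How AEs are found.** Adverse event reporting and harms {22} defines an AE as "any undesirable experience occurring to a subject during the study, whether or not considered related to BLT". It names two sources. The first is unsolicited: "All AE reported spontaneously by the subject or observed by the investigator, or their staff will be recorded". The second is solicited: "Additionally, a weekly screening of AE will be conducted". No arm is excluded from the screening, and no end date is given for it.

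**Staff contact.** Under The LightCafé Approach, each session "includes 5–10-min consultations with a professional nurse or psychologist". For Light@Home, Explanation for the choice of comparators {6b} says only "Patients receive BLT in their own homes". In all arms sessions are "lasting 30 min each, are scheduled from Monday to Friday between 7:30 AM and 10:30 AM" (Intervention description {11a}), for one to three weeks depending on the QIDS-SR.

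**When the AE scale is given.** Table 1 lists the scale ("Occurrence and severity of adverse events") with one mark, under the treatment Evaluation. There is no mark at Intake, B1, PT1, F1 or F2. The description of the scale under {18a} names headache, eyestrain and nausea as examples and sets its purpose as monitoring tolerability while the intervention is running. The Treatment phase section places tolerability and mania assessment after each treated week. Of the QIDS-SR, by contrast, the same section says "Every Friday, depressive symptoms are assessed using the QIDS-SR, regardless of whether the participant received treatment that week". It says nothing of this kind about the AE scale.

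**The concern.** Three features of the schedule limit what the harm data can show.

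1. Unsolicited reports rise with the number of occasions on which someone is there to hear or notice a complaint. Two arms have such an occasion at every session by design; for the third none is described. If the two sources are pooled in one table by arm, the table reflects contact frequency as well as harm.
2. If the scale is tied to treated weeks, the number of solicited assessments depends on a post-randomisation response. Early remitters are asked once, others up to three times. Untreated weeks are not covered, although the AE definition includes them.
3. Without a pre-treatment scale, a headache reported on the first Friday may be old or new.

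The trial compares ways of delivering the same light treatment and hopes to inform guidelines, so tolerability by arm is of real interest. There is no data monitoring committee and no auditing, so these AE records are the main safety evidence that the article describes.

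**Working it through.** The plan states no figure on this point, so there is none to reproduce. The check counts scheduled contacts and forms, then brackets the possible size under stated assumptions.

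**Step 1. Contacts and forms by weeks of treatment**

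Inputs: 5 sessions per week for 1 to 3 weeks ({11a}); one consultation per LightCafé session; one AE scale per treated week (Treatment phase, {18a}, Table 1). Coverage assumes that each scale looks back over one week, since no recall period is given. PT1 is at 4 weeks; F2 is at 4 months, taken as about 17 weeks.

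| Weeks treated | Session contacts, LightCafé arms | Session contacts described, home | AE scales, any arm | Share of 4 weeks to PT1 | Share of about 17 weeks to F2 |
|---|---|---|---|---|---|
| 1 | 5 × 1 = 5 | none | 1 | 1/4 = 25% | 1/17 = 5.9% |
| 2 | 5 × 2 = 10 | none | 2 | 2/4 = 50% | 2/17 = 11.8% |
| 3 | 5 × 3 = 15 | none | 3 | 3/4 = 75% | 3/17 = 17.6% |

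For a given treatment length the number of solicited scales is the same in every arm. The arms differ only in the contact columns.

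**Step 2. What the contact difference could do**

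Assume the same true AE risk p = 30% in every arm. The weekly screen finds a fraction s of events, and daily contact picks up a fraction u of those missed. Then

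- detected at home = p × s
- detected in a LightCafé arm = p × [s + (1 − s) × u]
- apparent risk ratio = 1 + (1 − s) × u / s, in which p cancels.

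| s | Home | LightCafé, u = 0.25 | LightCafé, u = 0.50 | Risk ratio |
|---|---|---|---|---|
| 0.60 | 18.0% | 21.0% | 24.0% | 1.17 to 1.33 |
| 0.80 | 24.0% | 25.5% | 27.0% | 1.06 to 1.13 |
| 0.95 | 28.5% | 28.88% | 29.25% | 1.01 to 1.03 |

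All of p, s and u are assumptions; the article gives none of them.

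**Step 3. What response-dependent screening could do**

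Assume a 15% AE risk per week. The cumulative risk is 0.150 after one week, 1 − 0.85² = 0.2775 after two and 1 − 0.85³ = 0.3859 after three. Take two assumed stopping patterns over weeks 1/2/3:

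- 40/30/30%: 0.40 × 0.150 + 0.30 × 0.2775 + 0.30 × 0.3859 = 25.9%
- 15/25/60%: 0.15 × 0.150 + 0.25 × 0.2775 + 0.60 × 0.3859 = 32.3%

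The gap is 6.4 points, and its meaning depends on where the events come from. If the 15% is a background risk that continues off treatment, both arms truly have 38.6% over three weeks and the whole gap is missed events. If all events are caused by light and cease with it, the whole gap is a real difference in exposure and none of it is missed. The share due to ascertainment is therefore anywhere from 0 to 6.4 points on these inputs.

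**Step 4. The passages side by side**

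{22} gives a weekly screen without an end and an AE definition that runs through the study. The Treatment phase section, {18a} and Table 1 place the only listed instrument in treated weeks. The Evaluation column also holds the QIDS-SR, which continues off treatment, so Table 1 alone does not settle whether the AE scale continues too. The wording in the other two places favours treated weeks only.

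**The case against.** **The safeguard common to all arms.** A reader might infer that AEs are not actively sought at home. The documents do not support that: the weekly screening has no arm limit, and the YMRS, a clinician interview, follows each treated week in every arm. This stands, and it confines the arm inequality to unsolicited events.

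**Silence is not zero.** That home patients have no staff contact at sessions is inferred from a condensed article. Section {18b} says personal contact is kept up with participants during the study. It gives no frequency and no AE purpose, so it does not equalise the arms, but it does rule out reading the home arm as unobserved.

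**The end of the scale is inferred.** {22} sets no end to the weekly screen, so one cannot state as fact that it stops with treatment. What stands is that the sections need reconciling.

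**No known net direction.** It is tempting to conclude that home treatment will look safer. More contact would raise counts in the LightCafé arms, but faster remission would lower the number of scales there, and the sample size section assumes larger effects in those arms. The two may partly offset each other.

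**Baseline and randomisation.** The missing B1 scale does not bias a randomised contrast, because pre-existing symptoms balance in expectation. It costs attribution and precision.

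**No AE test is stated.** The article plans no between-arm test of harms, and tabulation is commonly left to the analysis plan. This stands too. The point here is the collection schedule, which the article does state and which later analysis cannot repair. The contact difference is part of the intervention and cannot be removed, only kept separate in reporting.

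**Conclusion.** The point holds in a limited form. Spontaneous and staff-observed AEs have unequal opportunity by arm: 5 to 15 session contacts in two arms against none described at home sessions. The solicited scale is the same in all arms per treated week, but on the most natural reading it is given 1, 2 or 3 times according to response, and it has no pre-treatment value.

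The size of any distortion is unknown. For the contact difference it depends on how much the common weekly screen captures: negligible if that is about 95%, an apparent risk ratio of up to 1.33 if it is 60% and half of the missed events surface through contact. The 6.4-point illustration for screening length should not be read as bias, because it mixes real exposure with ascertainment. All these figures rest on assumed inputs. This is a cheap improvement to the harm data, not a defect in the primary comparison.

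**What to change.** 1. Reconcile {22} with the Treatment phase section, the scale's description in {18a} and Table 1. State that the existing AE scale is given at B1 and on every Friday of weeks 1 to 3 to all participants, whatever their treatment length, together with the QIDS-SR that already goes out on those days.
2. Base any between-arm harm summary on this scale, counting symptoms that are new or worse than at B1 over the fixed three-week window.
3. Report spontaneous and staff-observed AEs by arm in a separate table, with a note that contact frequency differs by arm. They should not be withheld from comparison, since they may include events that the checklist misses.

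**Cost.** One extra form at B1 for everyone, plus two for those treated for one week (1 + 2 = 3), one for those treated for two (1 + 1 = 2) and none for those treated for three (1 + 0 = 1). This assumes the checklist can be sent with the other questionnaires; staff administration would cost more. Recruitment began in February 2024, so the added forms cannot be recovered for participants already past these time points. The fixed-window summary would apply to later participants, and the report should say so.
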